## Statistical analysis plan

Descriptive statistics will be used to summarise the baseline demographic and clinical variables. For continuous variables, if the data are normally distributed, the mean and standard deviation will be calculated. If the data are not normally distributed, the median and interquartile range will be calculated. For categorical or binary variables, these will be summarised as frequency and percentage of total. There will be a variety of data consistency and quality checks performed at various stages of the data capture process, e.g. regular calibration and monitoring of measuring instruments, use of control standards in assays. All extreme values (mean +/- 3* standard deviation) and improbable values, as defined by clinical opinion will be investigated. In depth descriptions of these procedures exist in the trials data management plan, data management procedure and the data validation plan (code book) held by the sponsor. Outcomes assessors and statisticians will be blinded to trial arm until completion of analysis.

### Primary outcome

We will summarise, by group, any patients who were randomised, but did not have surgery, and reasons (i.e. death or withdrawal). We will also summarise by group the time between randomisation and surgery. Competing-risks survival regression will be used to model length of hospital stay. This allows for the fact that the participant may die in hospital, thus preventing the occurrence of the event of interest (discharge from hospital). As the time between randomisation and surgery will vary between participants, this will be included in the model. A multivariate model analysis will also be performed adjusting for clinically prognostic factors including age, gender, tumour type, T-stage and neoadjuvant treatment (yes/no). As a secondary analysis, we will perform the above including an interaction term in the model in order to test whether the effect of exercise differs according to whether psychological support is provided or not, although it is recognised that the power to detect any significant interactions in this number of patients will be low.

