### Recruitment and randomisation

Consecutive, potentially eligible patients will be identified at MDT meetings and approached with patient information sheets at surgical/oncological outpatient clinic appointments. If the patient chooses to participate in this trial, they will undergo a screening CPET. This constitutes part of standard clinical care in some NHS hospitals. Once reviewed by a senior clinician, final eligibility is confirmed, and written informed consent can be obtained for trial participation.

Patients will be randomised 1:1:1:1 to one of four groups. The study design is a 2 x 2 factorial design. The randomisation will be performed using
ALEA
^TM^
 from FormsVision, an online software not under the control of the study team. Patients will be randomised by ALEA
^TM^ by minimisation to the multimodal interventions or the control arm and stratified according to tumour type, hospital site, gender, neoadjuvant cancer therapy and age. Group 1 is control (routine care), group 2 is exercise alone, group 3 is psychological support alone and group 4 is a multimodal exercise, and psychological support.

WesFit began recruitment in April 2018 and at the time of publishing was paused due to coronavirus disease 2019 (COVID-19) lockdown restrictions.

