### Interventions

**Exercise intervention:** The exercise-training programme is consistent with the FITT principle (frequency, intensity, time and type), as advised by a panel of international experts and patient representatives. The exercise intervention has been shown by our group to be safe, feasible and tolerable in locally advanced rectal cancer patients following neoadjuvant chemoradiotherapy.
^
34,
45
^ Patients will participate in a prescribed, supervised, aerobic high-intensity interval, structured, responsive, exercise training programme (SRETP) on an electronically-braked cycle ergometer (Ergoselect Cloud bike). Participants will undertake 3-sessions per week (2-sessions per week if undergoing neoadjuvant treatments), from recruitment to surgical resection. These will occur within community gymnasia, unless precluded by safety concerns due to clinical condition. High-risk patients can exercise within a hospital setting. The high-intensity interval training (HIIT) comprises of an initial 5 minutes of unloaded pedalling. This is followed by 3 minutes at moderate intensity and 2 minutes at severe intensity. Moderate intensity exercise refers to the patient’s power output at 80% of oxygen uptake (VO
_2_) at the anaerobic threshold, (80%AT) derived at baseline CPET. Severe exercise intensity occurs at the patient’s power output, at 50% of the difference between the VO
_2_ at AT and VO
_2_ Peak (50%∆) also accounting for 2/3 of the ramp work rate. These 5-minute intervals will be repeated 6 times, followed by 5 minutes of unloaded pedalling. The entire session lasts for 40 minutes. If the patient is receiving neoadjuvant treatment the entire session lasts for 30 minutes, with the 5-minute intervals repeated 4 times rather than 6 times. The full exercise programme is reported according to the Template for Intervention Description and Replication (TIDiER) checklist for exercise. The checklist is available in
*Extended data*.
^
62
^

As part of the exercise intervention personal trainers delivering the supervised exercise intervention will receive training in behaviour change support in the form of Healthy Conversation Skills (HCS). HCS is a brief intervention, developed to equip health and social care practitioners with the skills to support improvements in diet and physical activity in their patients/clients.
^
50

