## Primary outcome

Length of stay is defined as the number of days a patient stays in hospital following surgery. It is calculated by subtracting the date of surgery from the date of discharge. The date of surgery is defined as day 0 of a patient’s post-operative hospital stay.

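### The primary length-of-stay model conditions on time from randomisation to surgery, a post-randomisation interval, which can bias the treatment effect if an intervention changes the wait

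*Protocol article*

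**What the plan says.** The Primary outcome paragraph under Statistical analysis plan names the method: "Competing-risks survival regression will be used to model length of hospital stay". Discharge is the event and in-hospital death the competing event. It then adds the covariate: "As the time between randomisation and surgery will vary between participants, this will be included in the model". That variation is the only reason given.

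A model with prognostic factors is described next as a further analysis: "A multivariate model analysis will also be performed adjusting for clinically prognostic factors including age, gender, tumour type, T-stage and neoadjuvant treatment (yes/no"). The interval therefore belongs to the main primary model, and the article describes no primary analysis without it. The same paragraph plans a descriptive check: "We will also summarise by group the time between randomisation and surgery".

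Three other statements matter here:
- On length of stay, the Primary outcome section under Outcome measures says: "It is calculated by subtracting the date of surgery from the date of discharge".
- On exercise, Interventions says: "Participants will undertake 3-sessions per week (2-sessions per week if undergoing neoadjuvant treatments), from recruitment to surgical resection". Counselling is offered weekly, also before surgery.
- On randomisation, the minimisation is "stratified according to tumour type, hospital site, gender, neoadjuvant cancer therapy and age".

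**The concern.** Randomisation balances what exists when it takes place. Time to surgery does not yet exist then; it is realised afterwards, while the interventions are being given. Putting it in the model compares patients who had the same wait, and the wait may itself depend on arm.

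Two things can then go wrong:
1. If an intervention affects length of stay partly by changing the timing of surgery, adjustment removes that part of the effect.
2. If unmeasured factors such as frailty or treatment toxicity cause both a long wait and a long stay, then at equal waits the arms are no longer alike on those factors. A difference can appear where there is none.

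The stated reason does not call for the adjustment. The outcome clock starts at surgery, so variation in the earlier interval does not distort the time scale. At stake is the primary effect estimate for either intervention.

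**Working it through.** **Text.** The interval starts at randomisation and ends at surgery. Exercise fills it, and counselling is offered within it. The article does not say that surgery dates are set before randomisation or independently of arm. It describes blinding for outcome assessors and statisticians only. So the article does not exclude an arm difference in waiting time, and it does not show one either.

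**Inputs.** From the article: N = 1560, 20% drop-out, control median 7 days, design HR 1.17. Evaluable patients: 1560 × 0.8 = 1248, split 1:1 for a factorial main effect. The planned N does not bear on this point.

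Assumed, because the article gives no values: a shift *d* in waiting time between arms (in SD), and an unmeasured cause with correlation *r* with waiting time and log-hazard effect *b* per SD on discharge. A negative *b* means a longer stay.

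**Formula under a true null.** Given arm and wait, the expected value of the unmeasured cause is r × (wait − d × arm). The arm coefficient therefore picks up about −r·b·d, and the adjusted HR is about exp(−r·b·d). Example: r = 0.5, b = −0.5, d = 0.25 gives exp(0.0625) = 1.064.

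**Simulation.** Cox model for discharge, true HR 1.00, 1248 patients, 1000 replicates per row, two-sided 5% test, no in-hospital deaths (a simplification).

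| r, b | d | Formula HR | HR with interval (rejection) | HR without (rejection) |
|---|---|---|---|---|
| 0.5, −0.5 | 0 | 1.000 | 1.002 (5.7%) | 1.002 (5.2%) |
| 0.5, −0.5 | +0.25 | 1.064 | 1.056 (15.9%) | 1.001 (5.0%) |
| 0.5, −0.5 | +0.5 | 1.133 | 1.115 (45.5%) | 1.001 (5.3%) |
| 0.5, −0.5 | −0.25 | 0.939 | 0.947 (15.6%) | 1.000 (5.9%) |
| 0.3, −0.3 | 0 | 1.000 | 0.999 (4.8%) | 0.999 (4.5%) |
| 0.3, −0.3 | +0.25 | 1.023 | 1.020 (6.5%) | 0.999 (4.6%) |
| 0.3, −0.3 | +0.5 | 1.046 | 1.039 (8.1%) | 0.996 (4.4%) |
| 0.3, −0.3 | −0.25 | 0.978 | 0.977 (8.0%) | 0.998 (6.6%) |

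A separate run (4992 patients, 60 replicates; r = 0.5, b = −0.5, d = −0.5) gave an adjusted HR of 0.897, the low end of the range. An HR above 1 means faster discharge, so under these assumptions a lengthened wait favours the intervention and a shortened wait counts against it.

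**Scale.** ln(1.17) = 0.157. A spurious 1.056 is ln(1.056)/0.157 = 0.0545/0.157, or 35% of the design effect. A spurious 1.115 is 0.1089/0.157, or 69%.

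**Effect acting through timing.** Suppose 0.05 of a total log-HR of 0.157 acts through the wait. Adjustment leaves 0.107, and exp(0.107) = 1.113. Simulated: HR 1.169 without the interval and 1.113 with it; power 78.5% and 42.9%.

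**The case against.** The strongest reply is that the bias needs the arms to differ in waiting time, and the article never says the interventions move the surgery date. Sessions are fitted into the time available. With no shift, the table shows that adjustment does no harm. This stands, and it limits the point to a possibility.

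The size can also be far smaller. The trial mixes surgery-alone and neoadjuvant patients, so much of the variation in waiting may come from a pathway known at randomisation. A further simulation used the stronger cause within each pathway, with assumed values of 40% neoadjuvant, mean waits of 140 and 35 days, and within-pathway SDs of 28 and 14 days. Shifts of 3, 7 and 14 days gave null HRs of 1.00, 1.01 and 1.02, with 4% to 6% rejection. These inputs are no better documented than the others, and together they show that the size is undetermined. The reassurance also weakens in a model that keeps the interval and adds neoadjuvant treatment. There the relevant scale is the within-pathway SD, on which 14 days is 14/28 = 0.5 or 14/14 = 1.0 SD.

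The by-group summary would let an arm difference be seen. That helps readers, but it does not repair a primary estimate already conditioned on the interval. The article also leaves open whether the interval enters as a covariate or a stratum; either form conditions on it.

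A reader might extend the point to T-stage in the further model. The article does not support that. T-stage is listed among "clinically prognostic" factors alongside baseline items, and nothing says that re-staged or pathological stage is meant.

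**Conclusion.** The point holds as a conditional one. The primary model conditions on a post-randomisation interval that spans the intervention period, for a reason that does not require it. If an intervention shifts the interval, the primary effect can be biased.

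Size and direction are unknown. Under the assumed values with a true null, the adjusted HR lies between about 1.00 and 1.12 if the wait lengthens and between about 0.90 and 1.00 if it shortens. The simulated model without the interval stays at 1.00, with 4% to 7% rejection, in every scenario in the table. These ranges rest on the chosen shifts and shared-cause strengths and on a simulation without in-hospital deaths.

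A reader might infer that the randomised comparison is already lost, or that the trial will report a biased result. The article does not support either: without an arm difference in waiting time the bias is about nil. The case for change is that the plan makes validity depend on an assumption that randomisation otherwise makes unnecessary.

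**What to change.** Remove time from randomisation to surgery from the primary competing-risks model. Adjust instead for factors fixed at randomisation and already used in the minimisation: planned neoadjuvant therapy, tumour type, hospital site, age and gender, with the values recorded at randomisation. Keep the by-group summary of the interval. If the interval-adjusted model is wanted, report it as a labelled sensitivity analysis, with a note that it conditions on a post-randomisation variable.

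This changes one sentence and needs no new data and no change to the planned N. The downside is possibly a small loss of precision. In the simulations with a true HR of 1.17 and no arm difference in waiting, power without and with the interval was 66.8% and 68.5% for the stronger shared cause, and 71.3% and 71.5% for the weaker one. Baseline factors may recover some of that; whether they recover all of it was not calculated.

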## Estimation of sample size

From previous studies, the median length of stay in the control group is estimated to be 7 days. To detect a clinically meaningful difference of a (significance level to detect a hazard ratio of 1.17 when the control group median in-patient time is 7 days) 1 day reduction in LOS with 85% power, alpha = 0.05, a sample size of 1560 participants will need to be recruited over 3 years, with a one year follow-up period. The sample size allows for a 20% drop-out.

Sample size calculations for 2×2 designs are based on the two main comparisons (i.e. exercise vs. no exercise and psychological support vs. no support). The trial sample size is the larger of these 2 comparisons, so in this case, the sample size calculation is powered on the psychological support comparison. The sample size calculation assumes that there is no interaction between the interventions.

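### The primary-outcome analysis does not say which of its two models is primary, and neither names hospital site, a minimisation factor, so power may be forgone

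*Protocol article*

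**What the plan says.** Under Recruitment and randomisation, allocation is 1:1:1:1 by minimisation, "stratified according to tumour type, hospital site, gender, neoadjuvant cancer therapy and age".

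Under Statistical analysis plan, Primary outcome, two analyses of length of stay are described. The first is a competing-risks regression in which time from randomisation to surgery is the only covariate named. The second is introduced as an addition: "A multivariate model analysis will also be performed adjusting for clinically prognostic factors including age, gender, tumour type, T-stage and neoadjuvant treatment (yes/no". Neither is designated as the primary analysis.

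Under Secondary outcomes, an optional adjusted analysis of disability-free survival refers back to the same factor list. Hospital site appears in no model in either section.

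Under Estimation of sample size, the design is a "hazard ratio of 1.17 when the control group median in-patient time is 7 days", with 85% power, alpha 0.05 and 1560 participants. "The sample size allows for a 20% drop-out".

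**The concern.** Minimisation forces the arms to be alike on the chosen factors. If those factors predict length of stay, the treatment estimate varies less from trial to trial than a model without them assumes. Its standard error is then too large and its test conservative. In a hazard model, leaving out a prognostic factor also pulls the estimate toward 1 relative to the hazard ratio within levels of that factor. Both effects cost power.

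The eligible operations span thoracic, colorectal, oesophagogastric, urological, head and neck, and hepatobiliary surgery, so tumour type may well be strongly prognostic. Site was thought important enough to balance on. With two primary-outcome models and no stated order between them, the reader also cannot tell which result decides the trial.

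**Working it through.** **1. Factors side by side**

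| Factor | Minimised on | First model | Additional model |
|---|---|---|---|
| Tumour type | yes | not named | yes |
| Hospital site | yes | not named | not named |
| Gender | yes | not named | yes |
| Neoadjuvant therapy | yes | not named | yes |
| Age | yes | not named | yes |
| T-stage | no | not named | yes |
| Time from randomisation to surgery | no | yes | not stated |

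**2. The plan's own figure**

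Inputs from Estimation of sample size: HR 1.17 (7/6 = 1.167), power 85%, alpha 0.05 (sidedness not stated, two-sided assumed), 20% drop-out. Each factorial main effect is a 1:1 comparison.

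- Schoenfeld events: 4(z₀.₉₇₅ + z₀.₈₅)² / (ln HR)² = 4(1.960 + 1.036)² / 0.1570² = 1457.
- With drop-out: 1457 / 0.8 = 1822, so 1560 is not reproduced.
- Evaluable from 1560: 1560 × 0.8 = 1248.
- Power at 1248 discharges: Φ(½√1248 × 0.1570 − 1.960) = Φ(0.813) = 79%. At HR 7/6 it is 78%; at one-sided 0.05 with HR 1.17 it is 87%.

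So 79% is the benchmark for a fully efficient two-sided analysis.

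**3. Simulated effect of leaving factors out**

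The documents give no site variation and no prognostic strengths, so these are assumptions: ten sites, exponential stays, no in-hospital deaths (the competing-risks model then reduces to Cox), allocation nearly balanced within site and across risk, conditional HR 1.17, n = 1248, two-sided 0.05. SDs are on the log-hazard scale.

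Site effect only:

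| Site SD | Without site: HR, power | Stratified by site: HR, power | Power difference |
|---|---|---|---|
| 0 | 1.169, 77.3% | 1.169, 75.5% | −1.8 |
| 0.2 | 1.165, 77.4% | 1.171, 78.0% | 0.6 |
| 0.3 | 1.160, 73.9% | 1.171, 78.0% | 4.1 |
| 0.5 | 1.144, 65.5% | 1.170, 76.1% | 10.6 |

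Other four factors combined as one score with SD 0.5 (800 replicates; Monte Carlo SE of a power near 78% is √(0.78 × 0.22 / 800) = 1.5 points):

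| Site SD | No factors | Four, no site | All five | All five minus none | All five minus four |
|---|---|---|---|---|---|
| 0.2 | 1.137, 61.5% | 1.165, 76.9% | 1.172, 78.9% | 17.4 | 2.0 |
| 0.3 | 1.130, 59.8% | 1.155, 72.8% | 1.167, 77.1% | 17.3 | 4.3 |
| 0.5 | 1.126, 56.1% | 1.146, 67.1% | 1.173, 78.7% | 22.6 | 11.6 |

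The one- to two-point differences are close to simulation noise.

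**4. Standard errors under the null** (SDs 0.5 and 0.3, 1200 replicates, Monte Carlo SE about 0.6 points)

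| Model | Empirical SE / model SE | Type I error |
|---|---|---|
| No factors | 0.90 | 2.8% |
| Four, no site | 1.01 | 4.6% |
| All five | 1.05 | 5.4% |

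The first row agrees with theory: 2[1 − Φ(1.96 / 0.90)] = 2.9%. The conservatism is clear for the model with no factors. The four-factor model is not distinguishable from 5%.

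**5. If 1.17 is a whole-group hazard ratio**

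With SDs 0.5 and 0.3 and a conditional HR of 1.213, the model with no factors gives HR 1.16 and 78% power; all five factors give 1.21 and 92%.

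**The case against.** The case against is substantial, and much of it stands.

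- **A reader might infer that the primary model omits every minimisation factor.** The text does not support that. Neither model is labelled primary, and the plan commits to a model with four of the five factors. Only site is missing from both.
- **The factor list is open-ended.** It is worded so that it could admit site, and a condensed article may leave the full list to an analysis plan not shown here. But the article does state models and covariates. The list it states adds a factor not used in allocation and leaves out one that was. Open wording permits site without committing to it.
- **A reader might infer that the hazard ratio is biased toward 1.** That holds only against a conditional HR. The design value comes from group medians of 7 and 6 days, which suggests a whole-group contrast; on that reading the estimate without factors is not shown to be attenuated (step 5).
- **A reader might blame the covariates for missing 85% power.** On a two-sided reading, 1248 evaluable patients give about 79% even with full adjustment. That shortfall belongs to the sample-size calculation.
- **A reader might quote a large loss from ignoring tumour type.** With six strata and assumed medians of 3.4 to 14.6 days, power is 67% unadjusted against 78% stratified. The spread is assumed, and the additional model already includes tumour type, so this is a gap between two planned analyses and says nothing about site.
- **There is no false-positive risk here.** The error is in the conservative direction. Statisticians are also to stay blinded until analysis is complete, which limits result-driven choice between models, though it does not say which one decides.

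**Conclusion.** The point holds in a limited form. Neither model is named as primary, the first names no minimisation factor, and site is named in none. Where omitted factors are prognostic, the result is over-large standard errors and power forgone.

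The size cannot be derived from the documents. Under the assumptions above, omitting site alone costs about 1 to 4 points at site SD 0.2 to 0.3 and about 11 at 0.5. With the other four factors at SD 0.5, omitting all five costs about 17 points at site SD 0.2 to 0.3 and about 23 at 0.5. If site has no effect, nothing is lost by leaving it out. If 1.17 is a whole-group HR, the cost is still roughly 14 points forgone (92% against 78%), without bias against the design value.

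**What to change.** Before unblinding, name one primary model: a competing-risks regression with both factorial terms, adjusted for all five minimisation factors. Enter site as a stratum, fixed effect or frailty, with a stated rule for pooling very small sites, and age as continuous. Report the unadjusted model as a sensitivity analysis. The optional adjusted analysis of disability-free survival refers back to this list and should follow the change. Whether T-stage and time from randomisation to surgery stay in the model is not settled by this point.

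The cost is wording only: allocation already uses all five factors, so no new data, visits or patients are needed. There are two downsides. The hazard ratio becomes conditional on the covariates, and the report should say so. If sites do not differ, stratifying buys nothing and may cost a little (75.5% against 77.3% in the simulation with no site effect, near simulation noise).

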## Abstract

**Background: **Surgical resection remains the primary curative treatment for intra-cavity cancer. Low physical fitness and psychological factors such as depression are predictive of post–operative morbidity, mortality and length of hospital stay. Prolonged post-operative morbidity is associated with persistently elevated risk of premature death. We aim to investigate whether a structured, responsive exercise training programme, a psychological support programme or combined exercise and psychological support, delivered between treatment decision and major intra-cavity surgery for cancer, can reduce length of hospital stay, compared with standard care.

**Methods: **WesFit is a pragmatic
**, **2x2 factorial-design, multi-centre, randomised-controlled trial, with planned recruitment of N=1560. Participants will be randomised to one of four groups. Group 1 (control) will receive usual pre-operative care, Group 2 (exercise) patients will undergo 2/3 aerobic, high-intensity interval training sessions per week supervised by personal trainers. Group 3 (psychological support) patients are offered 1 session per week at a local cancer support centre. Group 4 will receive both exercise and psychological support. All patients undergo baseline and pre-operative cardiopulmonary exercise testing, complete self-report questionnaires and will be followed up at 30 days, 12 weeks and 12 months post-operatively. Primary outcome is post-operative length-of-stay. Secondary outcomes include disability-adjusted survival at 1-year postoperatively, post-operative morbidity, and health-related quality of life. Exploratory investigations include objectively measured changes in physical fitness assessed by cardiopulmonary exercise test, disease-free and overall mortality at 1-year postoperatively, longer-term physical activity behaviour change, pre-operative radiological tumour regression, pathological tumour regression, pre and post-operative body composition analysis, health economics analysis and nutritional characterisation and its relationship to post-operative outcome.

**Conclusions: **The WesFit trial will be a randomised controlled study investigating whether a high-intensity exercise training programme +/- psychological intervention results in improvements in clinical and patient reported outcomes in patients undergoing major inter-cavity resection of cancer.

**ClinicalTrials.gov registration: **NCT03509428 (26/04/2018)

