## Introduction

The number of new cancer cases per year is expected to rise to 23.6 million by 2030. Depending on the cancer cohort, major curative cancer surgery is associated with post-operative morbidity in up to 50% of gastrointestinal cancer patients and up to 60% in pancreatic cancer patients especially after neoadjuvant cancer treatments.
^
1–
3
^ Improved surgical, oncological and anaesthetic techniques, enhanced recovery pathways and perioperative care have delivered consistent improvements in length of hospital stay, in-hospital morbidity and readmission rates after major surgery. However, over half of patients over the age of 60 years after major abdominal surgery live with reduced functional capacity, physical fitness and quality of life (QoL), with a significant proportion never regaining pre-operative fitness or independent living.
^
4,
5
^ Our group have described the association between reduced pre-operative physical fitness
^
6–
11
^ (and its decline with neoadjuvant cancer treatments) and poor post-operative outcomes in upper and lower gastrointestinal cancer patients. Furthermore, we have reported on the associations between reduced physical fitness and reduced mitochondrial function,
^
12
^ QoL
^
13,
14
^ and physical activity
^
15
^ after cancer treatments before surgery. This is mirrored by others describing the associations of selected objectively measured fitness variables using cardiopulmonary exercise testing (CPET) and postoperative complications and length of hospital stay.
^
16
^ Moreover, a recent systematic review
^
17
^ also shows that higher preoperative physical activity levels were associated with shorted length of hospital stay and better postoperative (QoL), but not reduced postoperative complications. Interestingly, interrogating physical activity time preoperatively showed that patients who were regularly physically active had lower postoperative complications after colorectal surgery.
^
18
^ Although this is all intuitive, clinical trials in this area are heterogenous, provide a mixed picture with elusive pathophysiological explanations.

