### Eligibility criteria

Patients will be eligible for WesFit if they are over 18 years old and are scheduled to have major, intra-cavity cancer surgery with a curative intent. These are defined as thoracic, colorectal (including anal and neuroendocrine tumours), oesophagogastric (including neuroendocrine tumours), urological (including prostate, bladder and renal tumours), head and neck (including nasopharyngeal, laryngeal, pharyngeal and oral) and hepatobiliary (including pancreatic, gall bladder and neuroendocrine tumours). Treatment includes surgery alone or surgery combined with cancer treatments (including but not limited to neoadjuvant chemotherapy, chemoradiotherapy or immunotherapies). All patients deemed by the multidisciplinary team (MDT) as potentially curable or undergoing neoadjuvant cancer treatments with curative intent prior to restaging and surgery will be included.

Exclusion criteria includes patients with a tumour that is considered surgically non-resectable, having absolute or relative contraindications to completing a CPET,
^
49
^ patients unable to perform CPET due to other coexisting acute illness or conditions (e.g. lower limb dysfunction), patients declining surgery or planned neoadjuvant treatment, if their weight exceeds 160 kg and patients unable to give informed consent.

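### Neither length-of-stay model names baseline CPET fitness, a pre-randomisation predictor collected in essentially every patient; adding it is a free gain in power of unknown size

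*Protocol article*

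**What the plan says.** **Fitness as a predictor.** The Abstract states "Low physical fitness and psychological factors such as depression are predictive of post–operative morbidity, mortality and length of hospital stay". The Introduction cites "associations of selected objectively measured fitness variables using cardiopulmonary exercise testing (CPET) and postoperative complications and length of hospital stay".

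**When it is measured.** The Abstract says "All patients undergo baseline and pre-operative cardiopulmonary exercise testing". Under Recruitment and randomisation, patients who choose to take part come first to a test: "they will undergo a screening CPET". Confirmation of eligibility, written consent and randomisation follow. Eligibility criteria exclude "patients unable to perform CPET due to other coexisting acute illness or conditions", as well as patients with contraindications to the test. Near-complete baseline CPET data is therefore a fair inference.

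**How it is used.** The minimisation is "stratified according to tumour type, hospital site, gender, neoadjuvant cancer therapy and age"; fitness is not in that list. Under Statistical analysis plan, Primary outcome, the first competing-risks model names only the time from randomisation to surgery. The second model is "adjusting for clinically prognostic factors including age, gender, tumour type, T-stage and neoadjuvant treatment (yes/no"). The word that introduces this list leaves it open, but fitness is not named. Elsewhere CPET serves eligibility, exercise prescription, repeat assessment and exploratory outcomes.

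**The concern.** The trial is built on the premise that low fitness lengthens hospital stay. Its best-documented prognostic variable is already in the database before allocation, yet neither the allocation nor the stated analysis of the primary outcome uses it.

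In a proportional-hazards type of model, omitting a prognostic baseline covariate moves the treatment hazard ratio towards 1 relative to the hazard ratio conditional on that covariate, and it lowers power. What is at stake is efficiency, in a trial with little power to spare on its own figures. Pre-specification also matters: an open list allows fitness to be added or left out later, unless the statistical analysis plan, which is not shown, closes it.

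**Working it through.** **Inputs from the protocol article**
- Hazard ratio 1.17, control median 7 days, 1-day reduction, 85% power, alpha 0.05 (sidedness not stated), N = 1560, 20% drop-out (Estimation of sample size).
- 1:1:1:1 allocation (Recruitment and randomisation), hence 1:1 for each factorial main effect.
- Evaluable patients: 1560 × 0.8 = 1248, all taken as discharged alive.

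**Input not in the documents (assumed):** the discharge hazard ratio per SD of baseline fitness, taken as 1.1 to 1.5.

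**Step 1. The plan's own figure.** Schoenfeld events = 4(1.96 + 1.036)² / (ln 1.17)² = 1457 for two-sided 0.05 and 85% power. Dividing by 0.8 gives 1822 patients, so 1560 is not reproduced on these inputs. It is approached with 80% power (1274 events, 1593 patients), or with one-sided alpha and a hazard ratio of 7/6 (1211 events, 1514 patients). That is a separate matter. Here it only sets the starting point:

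Power at 1248 discharges = Φ(ln 1.17 × √(1248/4) − 1.96) = Φ(0.1570 × 17.66 − 1.96) = Φ(0.813) = 79.2%.

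At 1560 discharges with no drop-out it is 87.3%.

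**Step 2. Effect of leaving fitness out.** Simulation of 3000 trials per row: 1248 discharges, 1:1, conditional treatment hazard ratio 1.17, one standard-normal fitness covariate, Cox fits with and without it, two-sided 0.05. In-hospital deaths and all other covariates were ignored.

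| Assumed fitness HR per SD | Treatment HR, omitted → adjusted | Power, omitted → adjusted | Difference (points) |
|---|---|---|---|
| 1.0 | 1.170 → 1.170 | 78.9% → 78.9% | 0 |
| 1.1 | 1.168 → 1.170 | 77.7% → 78.5% | 0.8 |
| 1.2 | 1.166 → 1.172 | 77.1% → 79.1% | 2.0 |
| 1.3 | 1.159 → 1.170 | 73.9% → 79.1% | 5.2 |
| 1.5 | 1.150 → 1.172 | 68.7% → 79.6% | 10.9 |

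The Monte Carlo standard error of each power is about √(0.79 × 0.21/3000) = 0.7 points. A row at 2.0 gave 52.6% → 77.8%; it is not relied on.

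**Step 3. Check of the 1.5 row.** The squared ratio of mean log hazard ratios is 0.774, so omission acts like having 1248 × 0.774 = 966 discharges. Φ(0.1570 × √(966/4) − 1.96) = Φ(0.480) = 68.4%, in line with the simulated 68.7%.

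**Step 4. Chance imbalance.** With 624 per side, the SD of the difference in mean fitness is √(2/624) = 0.057 SD units. Multiplied by ln 1.2 = 0.182 this shifts the log hazard ratio by 0.010; multiplied by ln 1.5 = 0.405 it shifts it by 0.023. The target is ln 1.17 = 0.157.

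**The case against.** **The covariate list belongs in the statistical analysis plan.** The article condenses a fuller protocol, its list is open, and nothing in it excludes fitness. This stands in part: the unseen plan may already include fitness, and then nothing remains to be done. It does not dispose of the point, because the article does fix covariates for both models, and the first names only the randomisation-to-surgery interval.

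**No loss has been shown.** A reader might infer that the primary hazard ratio is biased, or that planned power is certainly eroded. The documents do not support that. The attenuation is non-collapsibility, not bias, and the test without fitness is valid under randomisation. The 1.17 also matches a ratio of whole-group medians (7/6 = 1.167), so it may be a marginal effect. In that case omission gives up a possible gain and does not reduce the planned power. The article does not say which kind of effect it is.

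**The size is assumed.** This stands. No effect of fitness on stay is given, and the simulation holds no other covariates. In the adjusted model, age, gender, tumour type and neoadjuvant treatment may already carry part of the fitness information, and the gain would then be smaller.

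**Chance imbalance.** A reader might also infer that an imbalance in fitness could pass for an exercise effect. At about 624 per side the typical shift is 0.010 to 0.023 against a target of 0.157, and the type I error rate already covers it. This is not a ground for the change.

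**T-stage.** It would be wrong to contrast fitness with T-stage as a factor without stated relevance, since the article itself lists T-stage as prognostic.

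**Conclusion.** The point holds as a missed, cost-free improvement and not as an error that invalidates the analysis. Baseline fitness is measured before randomisation in essentially all patients and is called a predictor of the primary outcome. It is absent from the minimisation factors and from the covariates named for both models.

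The size is unknown. It is about 1 to 11 points of power for assumed discharge hazard ratios of 1.1 to 1.5 per SD, and none if fitness has no effect. This rests on a conditional treatment hazard ratio of 1.17, two-sided 0.05, 1248 discharges, no in-hospital deaths and no other covariates. The 1-point end is about the size of the simulation error. If 1.17 is a marginal effect, the same omission is better described as power not gained. With about 79% power at 1248 discharges under two-sided testing, a gain of even a few points is worth having.

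**What to change.** Under Statistical analysis plan, Primary outcome (and in the statistical analysis plan, if it does not already do so):

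- Pre-specify one CPET variable, for example VO2 at the anaerobic threshold, chosen before unblinding. Enter it as a continuous covariate in both the primary and the adjusted competing-risks models.
- Use only the screening/baseline value obtained before randomisation. Do not use the pre-operative test or those repeated during neoadjuvant treatment, which the exercise programme may change.
- State a simple imputation rule for the few missing values, such as those where the threshold cannot be determined, so that no randomised patient is dropped for that reason.
- Report the estimate without fitness alongside.

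Cost: wording only. No new data, visits or patients are needed. If fitness adds nothing, the price is one degree of freedom. The reported hazard ratio becomes conditional on fitness, which is why the estimate without it should be shown as well.
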